### **3.2 Maintaining a Stock in and Stock out Record for the Purchase of Salt, Condiments, and Foods with High Salt Content, as well as A Record for the Number of Diners per Meal**

Nursing homes that are assigned to the SSSC group have to establish a stock in and stock out record for condiments and foods with high salt content, as well as a record for the number of diners per meal. They will also have to record this information truthfully on the standardized stock in and stock out record form and diner record form provided by the research group (see Annex 3).

Items that have to be recorded in the stock in form include:

- Table salt
- Condiments (e.g. soy sauce, chicken bouillon, MSG, fermented chili bean paste, chili paste, sweet bean sauce, etc.)
- Foods with high salt content (e.g. salted vegetables, pickled vegetables, preserved eggs, fermented vegetables, etc.)

- Processed foods (e.g. instant noodles, vermicelli, bread, sausages, etc.)

Purchasers have to keep a detailed record of the item type purchased, date, quantity, and number of items left on the purchase record form.

Salt and condiments have to be placed in locked storage rooms and managed by the purchasers. Cooks are not allowed to obtain these items on their own. If the condiments in the kitchen have been used up and needs to be replenished, the cook has to inform the manager about the type and amount of condiment needed. The purchaser will procure the required condiment from the storage room and replenish the stock in the kitchen. At the same time, the purchaser has to record the type, date, and quantity of the item that was taken out of the storage room in detail in the stock out form. Aside from that, a daily record of the number of diners in the nursing homes has to be kept (includes the elderly and staff).

The stock in, stock out, and number of diners will be recorded immediately after the randomization has been done and will end when the intervention is over.

### **3.3 Stepwise Salt Supply Control Plus Health Education**

➤ An extra and targeted health education will be supplied to nursing homes assigned to the SSSC group. Its aim is to increase the degree of compliance of the members of the nursing homes to the intervention measures and reduce the potential obstacles and resistance. This event will be executed by the personnel responsible for the SSSC intervention strategy from the sub-sites.

➤ Health Education Target Audience. Includes managers of nursing homes, purchasers, cooks, as well as the elderly living in the nursing homes for a prolonged period and their caretakers.

➤ health education activity.

1) An SSSC initiation meeting will be held in every nursing home and all personnel stated above will be invited. A standardized lesson will be conducted on the benefits of consuming less salt, the overall aim of the activity, etc;

2) A forum for the elderly will be held during the inspection once every 3 months to obtain feedback and opinions about the salt reduction intervention, as well as to launch the targeted

health education;

3) Release health education publicity materials during appropriate times: Such as promotional posters, pamphlets, etc;

4) Along with technical training, engage in targeted health education with the managers, purchasers, and cooks of the nursing home. Muster an subjective initiative to launch various salt reduction strategies on their own and increase the level of awareness and thought for the elderly's health.

#### **4. Salt Supply**

During the intervention period, the salt (regular salt and salt substitute) was uniformly produced and provided free of charge by suppliers designated by Peking University Clinical Research Institute. Suppliers have to ensure that they have a sufficient supply of the salt substitute during the intervention period, and there should not be a shortage and out of stock.

## 5.5 Follow-up

- Follow-up timings: 6, 12, 18, and 24 months after the randomization

Follow-up content: See the Table below.

- Follow-up method:

Questionnaire: Professional investigators who have undergone standardized training will read through and check the travel records and medication information of the nursing homes, as well as question the participants. The information will be further verified through the New Rural Co-operative Medical System.

Physical examination: A physical examination will be conducted on participants. Laboratory Examination: Participants will be required to empty their bladder and record the time in the morning. They will then be given a 24-hr urine bucket and urine cup to collect their urine over the next 24 hours. The urine collection will be stopped at the same time on the morning of the second day. The urine volume of the participants over 24 hours, left out situations of urine, and the start and end time of the collection will be recorded. After mixing the 24-hr urine sample thoroughly, 5ml of urine will be collected using a catheter and stored at -20°C. 4ml of venous blood will be collected from participants on an empty stomach on the morning of their physical examinations.

Research Follow-up Form

| 
Time
 
Items
                 | Preparation Period | Baseline | Follow-up Period |          |          |          |             |                                  | Early Withdrawal |
|--------------------------------------------------|--------------------|----------|------------------|----------|----------|----------|-------------|----------------------------------|------------------|
|                                                  |                    |          | Month 6          | Month 12 | Month 18 | Month 24 | At any time | Transferring to Another Hospital |                  |
| Signing of Informed Consent Form                 | √                  |          |                  |          |          |          |             |                                  |                  |
| Confirmation of Inclusion and Exclusion Criteria | √                  |          |                  |          |          |          |             |                                  |                  |
| Basic Information Page                           | √                  |          |                  |          |          |          |             |                                  |                  |
| Demographic Data                                 |                    | √        |                  |          |          |          |             |                                  |                  |
| Lifestyle                                        |                    | √        |                  |          |          |          |             |                                  |                  |
| Satisfaction in Meals                            |                    | √        | √                | √        | √        | √        |             |                                  | √                |
| History of Disease and Treatment                 |                    | √        |                  |          |          |          |             |                                  |                  |
| EuroQol Five Dimensions Questionnaire (EQ-5D)    |                    | √        |                  | √        |          | √        |             |                                  | √                |

Project Title: Evaluating the Efficacy, Safety, and Cost-Effectiveness of Using a Salt Substitute (SS) and Stepwise Salt Supply Control (SSSC) on Lowering the Blood Pressure of the Collective Aged Population

Project Protocol (Version Number: V1.4, Version Date: 2019-10-17)

|                                        |  |   |   |   |   |   |   |   |   |
|----------------------------------------|--|---|---|---|---|---|---|---|---|
| Height, Weight                         |  | √ |   |   |   | √ |   |   | √ |
| Blood Pressure, Heart Rate             |  | √ | √ | √ | √ | √ |   |   | √ |
| Blood Routine                          |  | √ |   |   |   | √ |   |   | √ |
| Blood Sugar, Four Items of Blood Lipid |  | √ |   |   |   | √ |   |   | √ |
| 24hr Urine                             |  | √ |   |   |   | √ |   |   | √ |
| Eye Fundus Examination                 |  | √ |   |   |   | √ |   |   | √ |
| Antihypertensive Drug Information      |  | √ | √ | √ | √ | √ |   |   | √ |
| Collection of Hospitalization Records  |  | √ |   |   |   |   |   | √ |   |
| Reports of Adverse Reactions           |  |   |   |   |   |   | √ |   |   |
| CRF Signature Page                     |  |   |   |   |   | √ |   |   | √ |

- Early Withdrawal from Trial
- Criteria for early withdrawal:
  1. Researchers determine that it is not suitable for the research to continue because of adverse events;
  2. Participants request to withdraw from the research;
  3. Going against the protocol and others.
- The reason for early withdrawal should be recorded for participants who withdraw from the trial after meeting the early withdrawal criteria. And the following examination items should be performed and recorded during the last visit to the best of the ability:
  - Laboratory examination: Blood routine, kidney function, blood sugar, blood lipid, 24-hr urine
  - Physical examination: Height, weight, blood pressure, heart rate
  - Information about antihypertensive drug consumption, satisfaction in meals
  - EuroQol Five Dimensions Questionnaire (EQ-5D)
  - Endpoint events, safety incidents
  - Monitoring and record of adverse events

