## **7.4 Serious Adverse Events**

A serious adverse event (SAE) is defined as having any of the following outcomes resulting from the intervention:

- Threat to life
- Requiring hospitalization
- Permanent or significant disability and dysfunction

Should an SAE occur during the course of the research, researchers must adopt the suitable treatment measure on the participant immediately and end the trial.

Should an SAE occur, researchers have to find out the details and record the following content, whether or not it has to do with the intervention strategies: Time of occurrence, end time, measures adopted, relationship with the investigational drugs, etc. For expected SAEs that are unrelated to the research, researchers have to conduct the appropriate recordkeeping and report it to the Ethics Committee after the research is over. For unexpected SAEs or SAEs that are related to the research, a report has to be made in accordance with the provisions of the Ethics Committee.

Should any adverse events occur, researchers have to record the following on the CRF: Time of occurrence, level of severity, end time, measures adopted, and outcome.

The severity of adverse events can be classified into the following 3 levels:

- Mild: Light symptoms and physical signs. Usually a one-off event that does not require treatment and will not affect daily activities. Symptoms would automatically be relieved with rest;
- Moderate: Symptoms and physical signs persist for a longer time. Slightly affects daily activities. Will recover with simple treatment;
- Severe: Symptoms and physical signs persist for an even longer period. Severely affects normal work and activities. Will not easily recover with simple treatment.

Researchers must immediately tend to adverse events that occur during the process of the research appropriately and in accordance with medical guidelines. Researchers can increase the number of follow-ups and laboratory tests on the participants if necessary. Follow-ups should be conducted until the adverse event is resolved or until the participant is in stable condition or fully recovers.

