## 9. Statistical Analysis

### **Baseline Data Analysis:**

Participants will be described with respect to demographic information (age, gender, ethnic group, education, etc.), anthropometrics (weight, height, BMI, etc.), physical examination (SBP, DBP, etc.), life style and diet habits, labs (serum potassium, renal function, urinary sodium, urinary potassium, urinary microalbumin, etc.), comorbidities, medication history at baseline, both overall and separately for the intervention and control groups. Categorical data will be summarized by numbers and percentages. Continuous data will be summarized by mean, SD and range if data are normal and median, IQR and range if data are skewed. We will conduct one-way ANOVA on continuous variables and  $\chi^2$  test on categorical variables to check if the baseline characteristics balanced across randomized groups and to identify potential confounding variables.

**Effect Evaluation:** Results from ITT analysis will be reported as the primary result and the one from PP analysis will be reported as the secondary result.

Primary outcome is the change in SBP from baseline to follow-up

Secondary outcome includes change in DBP from baseline to follow-up, changes in 24-hr urinary sodium and urinary microalbumin; the risk of developing cardiovascular events

We will use multilevel mixed-effects model to control the cluster effect and confounding variables. We will compare the difference of changes in blood pressure before and after the intervention between SS and non-SS, SSSC and non-SSSC, SS + SSSC and SS only or SSSC only respectively.

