## 10. Sample Size Calculation

The research hypothesis is that the "salt substitute intervention would significantly reduce the systolic blood pressure of patients with hypertension", with the test power of 0.80 and the significance level at 0.05. According to previous studies, consuming salt substitutes for a prolonged period can lower the systolic blood pressure of patients with hypertension by roughly 2~5mmHg. This research hypothesizes that the systolic blood pressure of the elderly participants would decrease by 3.0mmHg, with a standard deviation of 18mmHg. Since the number of groups is 48 and the intra-group correlation coefficient is 0.02, 16 participants are needed in every group calculated by NCSS-PASS software. In addition, considering that about 20% of the participants might be lost to follow-up or be removed from the research due to non-compliance, it is finally determined that 20 participants will be included in each nursing home, for a total of 960 participants across 48 nursing homes.

Based on the sample size calculated above, the sample size for the four intervention groups is as follows:

|                   |     | SS intervention |     |       |
|-------------------|-----|-----------------|-----|-------|
|                   |     | Yes             | No  | Total |
| SSSC intervention | Yes | 240             | 240 | 480   |
|                   | No  | 240             | 240 | 480   |
| Total             |     | 480             | 480 | 960   |

For the other intervention strategy, it can be estimated from the previous research experience that the SSSC intervention strategy can reduce the systolic blood pressure of the elderly by 4.0mmHg. With the significance level, number of groups, and intra-group correlation coefficient constant, and based on the sample size calculated above, it can be concluded that the power of applying this intervention strategy to reducing systolic blood pressure by 4.0mmHg will be 96.6%.

Given the potential changes of actual systolic blood pressure difference during the trial and the number of participants recruited from each facility, the changes to the trial power will follow the trend below:

[figure not shown]

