## 3. Statistical Principles

The analysis will be conducted by intention-to-treat.

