### 3.4 Missing data

No imputation will be conducted for primary analysis of primary outcome, secondary outcomes and safety outcomes.

For survival analysis, those who loses to follow-up will be regarded as right-censored and the censoring date will be the date of last encounter. If the date of occurrence of an event is not recorded, it will be imputed as the median of the date of last follow-up and the one when event reports.

For sensitivity analysis of SBP difference from baseline to 24-month SBP, 24-month SBP will be imputed using multiple imputation. The model will be:

$$Y_i = \beta_0 + \sum \beta_i X_i + e_i$$
$$e_i \sim N(0, \sigma_e^2)$$

Where  $Y_i$  is the SBP for subject  $i$  at month 24;  $\beta_0$  is the intercept;  $X_i$  is the variable for imputation;  $e_i$  is the random error.

Variables for multiple imputation of 24-month SBP includes SBP, DBP and pulse at baseline, 6 months, 12 months and 18 months, as well as residential facilities, center, age, gender, education, BMI, past history of hypertension, diabetes and coronary artery disease, lifestyle information, medication use in baseline and follow-up.

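### Residents can be withdrawn for non-adherence with only a closing visit, so the later SBP readings that an intention-to-treat analysis needs are not collected

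*Supplement*

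**What the plan says.** Protocol V1.4, section 5.5, gives three grounds for early withdrawal: "Researchers determine that it is not suitable for the research to continue because of adverse events"; the participant's own request; and "Going against the protocol and others". For anyone withdrawn, "the following examination items should be performed and recorded during the last visit to the best of the ability". Blood pressure is one of those items. No visit after that one is described. In the follow-up table the CRF signature page is ticked at month 24 and at early withdrawal and nowhere else. SAP Table 1 repeats this under its quit column.

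Section 10 of the protocol shows that such removals are expected: "about 20% of the participants might be lost to follow-up or be removed from the research due to non-compliance". SAP 2.5 describes the same 20% as loss to follow-up only.

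On analysis, protocol section 9 states "Results from ITT analysis will be reported as the primary result" and SAP section 3 states "The analysis will be conducted by intention-to-treat". SAP 3.3 admits a resident to the FAS for SBP, as randomised, if a baseline and at least one post-baseline SBP exist. Major protocol deviation is handled by exclusion from the per-protocol set (PPS). SAP 3.4 allows no imputation in the primary analysis.

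**The concern.** Intention-to-treat needs outcome data on everyone randomised, whether or not they adhered. The SAP already has a place for people who deviate, the PPS. If the protocol also stops measuring them, the primary analysis loses their later data as well, and the two analyses become harder to tell apart.

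The primary mixed model uses all available SBP and tolerates missing visits when the missingness depends only on what the model contains. Removal decided on non-adherence or an adverse event may depend on things it does not contain. The SAP already cites high mortality and departures from the homes as its reason for changing the primary outcome. Adding avoidable missingness to that is unwelcome.

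The loss could also be uneven between arms. Under section 7.1, when potassium is again above 5.5 mmol/L at the two-week review, an SS resident leaves the research, whereas a resident outside SS is treated and stays under monitoring. Under section 7.3, gastrointestinal reactions judged to be due to the intervention also end participation, which points to the intervention arms.

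**Working it through.** **1. The plan's own figure.** Inputs from protocol section 10: 16 evaluable residents per home, a 20% allowance and 48 homes.

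- 16 / (1 − 0.20) = 20 per home
- 20 × 48 = 960 in total
- 0.20 × 960 = 192 residents in the allowance, leaving 768 = 16 × 48

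The stated 20 and 960 reproduce exactly. The allowance therefore carries planned removals, mixed with ordinary loss. The split is not given.

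**2. What happens to a removed resident.** Take a resident withdrawn for non-adherence between months 6 and 12.

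- Scheduled SBP: month 6 is available; months 12, 18 and 24 are not provided for.
- Closing visit: a blood pressure is sought on a best-effort basis. The SAP model indexes SBP by follow-up month and does not say how an unscheduled closing reading enters.
- Analysis set: the resident stays in the FAS in the randomised arm, represented by early readings only.

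If the same resident is withdrawn before month 6 and no closing SBP is obtained, there is no post-baseline SBP and the resident leaves the SBP FAS.

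**3. Whether the SAP's other analyses recover this.** Multiple imputation of month-24 SBP is a sensitivity analysis (SAP 3.4 and 5.7). Its listed variables include neither adherence nor withdrawal reason. The flow-diagram reasons in SAP 4.1 are death, hospitalisation, temporary absence, quit and other, so removal by the investigator would not be visible.

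**4. Possible size.** The documents give no removal rates by arm and no SBP difference between removed and retained residents. As an illustration only, assume removed residents contribute nothing and differ from retained residents by g mmHg in both arms. Then

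shift in contrast ≈ (share removed, intervention − share removed, control) × g

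| Removed, intervention v control | g = 3 | g = 5 | g = 10 |
|---|---|---|---|
| 2% v 0% | 0.06 | 0.10 | 0.20 |
| 5% v 0% | 0.15 | 0.25 | 0.50 |
| 10% v 5% | 0.15 | 0.25 | 0.50 |
| 20% v 10% | 0.30 | 0.50 | 1.00 |
| 20% v 0% | 0.60 | 1.00 | 2.00 |
| equal shares | 0 | 0 | 0 |

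For scale, the target effect is 3.0 mmHg. With SD 18, ICC 0.02, 16 per home and 24 homes on each side of a factorial margin, the effective number per side is 24 × 16 / (1 + 15 × 0.02) = 384 / 1.30 = 295.4. The standard error is 18 × √(2 / 295.4) = 1.48 mmHg. The table overstates the shift where removed residents have earlier readings, because those stay in the model.

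**The case against.** The strongest reply is that the SAP already does most of what is needed. Withdrawn residents with one post-baseline SBP are kept as randomised, a closing blood pressure is sought, all available readings are used, deviators are excluded only from the PPS, and imputation is a sensitivity analysis. This stands in part: intention-to-treat is not contradicted as an analysis set. What it leaves open is that readings after removal are never taken.

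Several stronger readings are tempting, and the documents do not support them.

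- **Removal falls mainly on the intervention arms.** The non-adherence criterion names no arm. Compliance (protocol 6.3) and the prespecified violations (SAP 3.2) are defined for facilities. The adherence violations concern only SS and SSSC homes, which makes imbalance plausible, but the explicit arm difference is the potassium rule.
- **Any hospitalisation ends participation.** Section 7.4 says that after an SAE "researchers must adopt the suitable treatment measure on the participant immediately and end the trial". It does not say whether this means the participant or the whole trial. It defines an SAE by outcomes resulting from the intervention, although it also requires unrelated SAEs to be recorded. Follow-up runs until the event resolves or the participant is stable. The visit table has a hospital-transfer column separate from early withdrawal.
- **Deaths after removal are all lost.** SAP 3.4 says "those who loses to follow-up will be regarded as right-censored and the censoring date will be the date of last encounter", so a removed resident could be censored early if treated as lost. But nothing stops event ascertainment: homes keep exit records, information is checked against the rural medical insurance system, and the FAS for events needs no follow-up SBP.
- **The effect is overstated by 5–11%.** This comes from assuming that 5–10% of intervention residents are removed and have no benefit: 3.0 × 0.95 = 2.85 and 3.0 × 0.90 = 2.70, with 3.0 / 2.85 = 1.05 and 3.0 / 2.70 = 1.11. The rate is not in the documents. A removed resident may also go on eating from the same kitchen; if the full effect persists, this overstatement goes to about zero.

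**Conclusion.** The point holds as an avoidable gap in data collection that does not fit the stated intention-to-treat principle. Three facts carry it: non-adherence is a ground for withdrawal, only a closing visit follows, and section 10 budgets for the removals. That follow-up ends is a reading of the closing visit and the CRF sign-off; no sentence says so outright. Equally, no sentence provides for scheduled SBP afterwards.

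The missingness may be informative and may differ by arm. Neither the direction nor the size of any bias can be derived from the documents. Under the assumptions in the table it runs from about 0 to 2.0 mmHg against a 3.0 mmHg target. The upper end needs 20% removed on one side, none on the other and a 10 mmHg difference; moderate imbalances give a few tenths of a mmHg.

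**What to change.** - **Section 5.5:** remove protocol non-adherence as a reason to end follow-up. State that stopping the intervention does not end data collection. Scheduled SBP and event assessments continue to month 24 in the randomised arm unless consent is withdrawn, the resident cannot be traced, or the resident dies.
- **Section 10:** describe the 20% as loss to follow-up, as SAP 2.5 does.
- **SAP:** handle non-adherence only through the PPS. Add investigator removal, with its reason and by arm, to the flow diagram.
- **Sections 5.5, 7.1, 7.3 and 7.4:** reconcile these with the intention-to-treat and FAS definitions, without changing any clinical stopping rule. Each should say whether it stops the intervention, ends research participation, or both. Section 7.1 uses both ideas for raised potassium: one paragraph ends participation in the research, while another only stops the SS intervention. Section 7.4 should say what is meant by ending the trial.

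The cost is wording, plus a few extra assessments in homes the team already visits every 6 months.
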